## Abstract

**Background:**

Phenylketonuria (PKU) is a hereditary metabolic disorder caused by mutations in the phenylalanine hydroxylase (*PAH*) gene, leading to the accumulation of phenylalanine (Phe) in the blood. Without timely treatment, PKU patients may develop irreversible intellectual and neurocognitive deficits. The primary treatment for PKU is a strict low-Phe diet, which must be initiated in early life to achieve better outcomes. Therefore, parents and parents’ caregivers play a crucial role in dietary management. However, poor dietary adherence and inadequate health knowledge significantly affect treatment efficacy. Mobile health (mHealth) interventions, as an emerging health management approach, offer personalized, low-cost, and highly accessible solutions. This study aims to develop and evaluate an mHealth intervention model based on the Behavior Change Wheel (BCW) theory and family health theory to improve health management for children with PKU.

**Methods:**

This single-center, single-blind randomized controlled trial will be conducted at the Inner Mongolia Maternity and Child Health Care Hospital in China from March to September 2025. Participants will include children with PKU and their parents’ caregivers, who will be randomly assigned to either the intervention group (receiving mHealth interventions via WeChat) or the control group (receiving routine health education). The intervention will include health education, dietary management, regular monitoring reminders, and online consultation services. The primary outcome will be the serum phenylalanine and tyrosine levels of the children. Secondary outcomes will include nutritional indicators, intellectual development indicators, and the caregivers’ health knowledge, compliance, and mental health. Data collection will occur at baseline and at 3 and 6 months post-intervention.

**Discussion:**

By integrating the BCW and family health theories, this study innovatively develops an mHealth-based health management intervention model for PKU. This model is expected to enhance family health management capabilities and improve clinical outcomes and quality of life for children with PKU. If effective, this model can be extended to other regions to provide more convenient and efficient health management solutions for PKU patients.

## Introduction

1

Phenylketonuria (PKU) is an inherited metabolic disorder caused by pathogenic mutations in the phenylalanine hydroxylase (*PAH*) gene, leading to decreased *PAH* activity and increased blood levels of phenylalanine (Phe) in the blood. Based on blood Phe concentrations, PKU can be categorized as moderate hyperphenylalaninemia (120-360 μmol/L), mild PKU (360-1200 μmol/L), or classical PKU (≥ 1200 μmol/L) according to the Rare Disease Diagnosis and Treatment Guidelines (2019).

In PKU patients, Phe builds up in the blood, cerebrospinal fluid, and brain, because it cannot be converted into tyrosine (Tyr). This can lead to varied degrees of irreversible intellectual and neurocognitive deficits if therapy is delayed (1). Globally, approximately 450,000 individuals are affected by PKU, with an average newborn prevalence of roughly 1 in 23,930 (2). Since 2009, PKU has been a required screening item in China’s Neonatal Disease Screening Management Measures. Affected infants’ prognosis can be greatly improved by early diagnosis by neonatal screening and subsequent low-Phe dietary intervention, which plays an essential role in lowering birth abnormalities and enhancing population health.

The main treatment for PKU is strict, long-term low-phenylalanine dietary therapy (3). When blood Phe levels are over 360 μmol/L, patients are advised to start a low-phenylalanine diet. Blood Phe levels should be regularly monitored to keep them between 120 and 360 μmol/L. Effective low-phenylalanine dietary management is, however, severely hampered by variables such poor dietary adherence, limited access to information on Phe content in foods, and low health literacy among patients and their parents, according to existing studies (4). Furthermore, the diet’s restriction raises the possibility of shortages in vital nutrients including vitamin B12, vitamin D, and folate, requiring frequent supplementation (5–7), which makes low-phenylalanine diet even more difficult.

The crucial role of parents and main caregivers is shown by the fact that early commencement of low-phenylalanine dietary therapy is essential for improved outcomes in PKU children. Few studies have examined the effects of interventions aimed at parents or main caregivers on health management among children with PKU, despite studies demonstrating that offering parents nutritional advice and skill training can improve the management of children who need special diets (8, 9). The blood Phe levels of PKU infants appear to be inversely correlated with parental understanding of PKU and dietary control, according to cross-sectional studies (10–12). Additionally, two intervention trials that focused on the main caregivers of children with PKU (4, 13) showed that health education combined with low-Phe dietary management is more successful than dietary intervention alone at lowering blood Phe levels.

However, traditional intervention methods for parents including in-person training sessions and written materials have limited scalability because of budget, time, and human resource limitations (14–17). Mobile health (mHealth), which have been extensively used in mental health, chronic illness management, and other fields, are becoming more and more important in modern health management, which provides more individualized, affordable, and accessible interventions (18). With the characteristics of easy to use, no need to additional download, and strong interactivity, WeChat can improve patients’ health outcomes, quality of life, and treatment compliance, while offering the possibility of individualized health management (19–23).

Susan Michie et al. developed the Behavior Change Wheel (BCW) theory in 2011 (24), which combines 19 behavior change theories to assist intervention planners in identifying obstacles to behavior change and creating the most effective comprehensive intervention plan. The BCW framework consists of three layers, as shown in **Figure 1**. The inner layer offers a thorough examination of the obstacles to changing one’s own behavior by examining the interaction of capability, opportunity, and motivation in shaping behavior (COM-B model). Nine intervention functions, education, persuasion, motivation, coercion, training, restriction, environmental restructuring, demonstration and empowerment, are identified by the intermediate layer to help direct the design of interventions. Seven categories for macro policy interventions are included in the outer layer to support the execution of intervention functions.

**Figure 1 f1:**
[figure not shown]
Schematic diagram of the Behavior Change Wheel (BCW) theory.

Additionally, Susan Michie et al. proposed a three-stage and eight-step procedure for putting the BCW theory into practice, which includes comprehending the behavior, choosing possible interventions, and establishing the content of the interventions to carry them out. The BCW theory has been widely applied in chronic disease management, dietary and nutritional management, health screening, medication adherence, and other health promotion studies (25–28). Several studies have successfully designed mHealth interventions using the BCW theory, showing positive outcomes (19, 29, 30).

Given that for children with PKU, parents are the primary factors influencing diet compliance and blood Phe control, this study combines the BCW theory with family health theory, targeting parents of PKU children as the main intervention subjects. Sharon Denham first innovatively proposed the concept of “family health” in 2003 (31). Weiss-Laxer et al. expanded on it by using the Delphi method to create a more thorough and methodical concept framework for “family health,” characterizing it as “A resource at the level of the family unit that develops from the intersection of the health of each family member, their interactions and capacities, as well as the family’s physical, social, emotional, economic, and medical resources” (32).

The family health concept framework was thoroughly examined in this study, as shown in **Figure 2**. Notably, family health is not simply the sum of individual health but encompasses six domains: Family relationships, interactions, and beliefs; Family social context; Family member health; Family health-related practices; Family health resources; Management of time and activities. These domains include both the sharing of internal family resources and the acquisition of external resources. These internal and external elements impact each family member’s health behaviors, awareness, and capacities through interactions, which in turn impacts the family’s overall health. Evidence suggest that family-centered health promotion programs play a significant role in primary, secondary, and tertiary prevention, and are effective and cost-effective in public health practice (33, 34).

**Figure 2 f2:**
[figure not shown]
Schematic diagram of the family health concept framework.

In conclusion, given that mHealth can effectively break through the time and space limitations and provide personalized intervention programs, this study aimed to develop a mHealth intervention model based on BCW and family health theory, which involved multiple intervention strategies such as improve the parents’ knowledge of PKU, follow a low-Phe die, regular monitor of blood and so on. It is hoped to provide a clinical basis for mHealth intervention to improve health management among children with phenylketonuria PKU.

Specific objectives are:

To evaluate the impact of the mHealth based on BCW and family health on clinical outcomes in children with phenylketonuria.To determine the effectiveness of the intervention program in improving health behavior management of children with phenylketonuria.

## Methods

2

### Trial design and setting

2.1

The research will be conducted at the Inner Mongolia Maternity and Child Health Care Hospital in China from March 2025 to September 2025, employing clinical reagent testing and internationally recognized scales for quantitative investigation.

The study population consists of families of children with PKU, who will be divided into two groups: Group A will be the mHealth intervention group, while group B was the control group. The intervention group will receive mobile health interventions through WeChat group chats. The control group, on the other hand, will simply get regular health education, which includes an oral presentation on PKU by a professional physician at the time of enrollment, educating the parents of PKU children on how to manage their diets low in phenylalanine. A printed handbook on PKU disease and daily management knowledge will also be given to them, but they won’t have access to online education and training, frequent reminders for monitoring, or online consultation services.

The intervention will last for 6 months, with clinical indicators, intelligence tests, and questionnaire surveys being conducted at baseline, as well as at 3 and 6 months after the start of the intervention to examine the effectiveness of the intervention on the health management of children with PKU. The flow chart of the study is shown in **Figure 3** and **Table 1**.

**Figure 3 f3:**
[figure not shown]
Flow chart of patient recruitment and study implementation.

**Table 1 T1:** Timeline for study enrollment, intervention, and evaluation.

Study Period	Recruitment	Intervention		Follow-up
Timepoint	-T1	0M	3M	6M
ENROLMENT: eligibility screen	✓			
Informed consent	✓			
ASSESSMENTS: sociodemographic variables		✓		
Anthropometric variables		✓	✓	✓
Intellectual development variables		✓	✓	✓
PKU knowledge		✓	✓	✓
Parents’ compliance with health management		✓	✓	✓
Parents’ mental health variables		✓	✓	✓
Family environment variables		✓	✓	✓

### Study participants

2.2

The participants of this study are all PKU children and their parents’ caregivers, such as parents, who meet the inclusion criteria and have been screened by the Inner Mongolia Maternal and Child Health Care Hospital in China by the end of February 2025. Each participant will begin the formal intervention after being informed face-to-face by a hospital doctor and signing the research informed consent form. This study has been approved by the Ethics Committee of Inner Mongolia Maternity and Child Health Care Hospital, Hohhot, Inner Mongolia Province.

Inclusion Criteria:

Age: 0 ≤ age < 12 years, regardless of gender.The child must meet the diagnostic criteria for PKU as outlined in the Rare Disease Diagnosis and Treatment Guidelines (2019) and be confirmed as a PKU patient through genetic testing.The parents’ caregivers, such as the child’s parents, must have the ability to use WeChat and possess normal language communication skills.They must understand and agree to participate in the intervention, be willing to fully cooperate with the intervention measures and follow-up examinations, and sign the informed consent form.

Exclusion Criteria:

The parents’ caregivers do not have a regular contact method or are unable to use WeChat daily.The child or parents’ caregivers have other severe systemic diseases or significant physical functional impairments.The child or parents’ caregivers exhibit mental symptoms such as unclear consciousness, language expression difficulties, or uncooperativeness.The child or parents’ caregivers are taking any psychiatric medications.The child or parents’ caregivers are already participating in other clinical trials.Any other reasons deemed unsuitable for participation in the trial.

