## Statistical analysis

3

Statistical analysis will be performed using SPSS Statistics 26.0. Categorical data will be expressed as counts and percentages (n, %). Continuous data will be presented as mean ± standard deviation (x¯ ± s). The Mann-Whitney U test will be used to compare changes in each indicator between the two groups at 3 months and 6 months post-intervention relative to baseline. The Wilcoxon test will be employed to compare differences between the two groups at baseline and across four follow-up time points. Baseline demographic characteristics between the two groups will be compared using the chi-square test. A two-tailed test will be applied, and a P-value < 0.05 will be considered statistically significant.

If a reasonable amount of missing data is present, the data summary will indicate that the data are missing at random. In such cases, all analyses will incorporate multiple imputation procedures using baseline variables as auxiliary variables to address missing data. Linear regression and logistic regression will be selected for the imputation process, and the final analysis results will be combined to complete the imputation and analysis procedures.

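### Eligibility from age 0 does not require that diet has begun, so some baseline Phe values may be pre-diet, and the unadjusted change-from-baseline test would lose precision

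*Protocol article*

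**What the plan says.** Section 2.2 (Study participants) gives the age criterion as "Age: 0 ≤ age < 12 years, regardless of gender". The child must meet the guideline diagnosis and "be confirmed as a PKU patient through genetic testing", and must "have been screened by the Inner Mongolia Maternal and Child Health Care Hospital in China by the end of February 2025". No criterion concerns time since diagnosis, whether a low-Phe diet is in place, or whether Phe has settled.

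The trial runs "from March 2025 to September 2025" with a 6-month intervention (section 2.1). The control arm also receives diet teaching at enrolment, "educating the parents of PKU children on how to manage their diets low in phenylalanine".

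The Introduction places mild PKU at 360-1200 μmol/L and classical PKU at 1200 or above. It says that above 360 "patients are advised to start a low-phenylalanine diet", and gives 120-360 as the range to hold.

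Section 2.4 describes a single random sequence without strata. Section 3 says: "The Mann-Whitney U test will be used to compare changes in each indicator between the two groups at 3 months and 6 months post-intervention". It names no covariate or stratum. Section 2.9 lists age at diagnosis and historical serum Phe among the clinical variables to be collected.

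**The concern.** The primary outcome is analysed as a raw change, so everything that moves Phe after month 0 enters the comparison. For a child already on diet, the change reflects the intervention plus ordinary variation. For a child whose month-0 sample precedes diet, it also contains the fall from diet start, which can be several times the planned difference of 100 μmol/L. That fall occurs in either arm, because both arms are taught the diet.

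Such children take the extreme ranks for a reason unrelated to the WeChat programme. With about 23 completers per arm and no stratification, the way a handful of them split between arms affects whether the trial detects a true effect. At stake are the power of the primary test and the readability of the mean ± SD summaries.

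**Working it through.** **The plan's own figure.** Section 2.3 uses a difference of 360 − 260 = 100, SD 100, two-sided α = 0.05 and power 0.90. The normal approximation is n = 2(1.960 + 1.282)² × (100/100)² ≈ 21.0, rounded up to 22. The exact two-sample t-test has power 0.8997 at 22 and 0.9125 at 23, so 23 per arm is reproduced. These inputs are concentrations, not changes.

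**From concentrations to changes.** With SD 100 at both visits and correlation ρ, SD of change = 100 × √(2(1 − ρ)). This is 118 at ρ = 0.3, 100 at ρ = 0.5 and 77 at ρ = 0.7. The document gives no ρ. With no pre-diet baselines, simulated power of the change-score Mann-Whitney at 23 per arm is about 0.78, 0.90 and 0.99 respectively. The figures below take SD of change = 100 unless stated.

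**Size of a diet-start fall.** For classical PKU reaching the top of the treated range, the fall is at least 1200 − 360 = 840 μmol/L. For mild PKU it lies between near 0 and 840. One fall of 840 moves an arm's mean change by 840/23 ≈ 37 μmol/L, over a third of the planned effect.

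**Power of the planned test by number of pre-diet baselines.** Simulation with 23 per arm, true effect 100, pre-diet baselines 1200-1800 (assumed), averaged over chance splits between arms:

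| Pre-diet baselines (of 46) | Pooled Mann-Whitney | Stratified rank test |
|---|---|---|
| 0 | 0.90 | 0.90 |
| 1 | 0.86-0.87 | 0.89 |
| 2 | 0.82-0.83 | 0.88 |
| 4 | 0.74-0.75 | 0.87 |
| 6 | 0.65 | 0.84 |

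**How much the split matters** (same model, pooled test):

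- One such child: 0.80 if in control, 0.93 if in intervention.
- Two: 0.85 if one per arm, 0.65 if both in control, 0.94 if both in intervention.
- Four: about 0.78 if two per arm, 0.54 if three are in control.

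Two such children land in the same arm with probability 22/45 = 0.49.

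**Different assumptions.** A second model draws pre-diet status at random, with baselines of 800 ± 300 or 1200 ± 400 and ρ = 0.5. Power is 0.87-0.88 at a 2% share, 0.81-0.84 at 5% and 0.73-0.74 at 10%. At a 2% share the loss is 1 to 5 points over ρ from 0.3 to 0.7. In this model a Mann-Whitney test on follow-up values alone keeps 0.88-0.90 at every share and every ρ. That model assumes newly started children reach the same follow-up level as the others.

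**How many such children?** The article does not say. If ages were spread evenly over 0-12 years (assumed), children under 2-3 months would be 2/144 to 3/144, or 1.4-2.1%. That is 0.7 to 1.0 child in 50.

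**The case against.** The strongest reply is that no passage says a newly diagnosed child's baseline precedes diet. Children must be diagnosed, genetically confirmed and screened by the end of February 2025, before a March start, and the Introduction stresses early diet. Such a child may well be on diet by month 0. This stands: the plan permits a pre-diet baseline but does not show one.

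It is also fair that a pool spanning twelve birth years probably holds few such children. On the even-age assumption there is about one, costing 2-4 points. That count covers only infants under 2-3 months, though. The criteria also admit an older child who was diagnosed late or is off diet at entry.

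A reader might infer more than this:

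- **That every newly diagnosed child falls by at least 840.** This applies only to classical PKU.
- **That the comparison is biased.** It is not: allocation is random, and simulated type I error stayed at 0.047-0.051 with 0 to 4 such children.
- **That power drops to 0.65 or lower.** That needs six or more such children in 46, which nothing in the document supports.

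The unknown correlation moves power more (0.78 to 0.99) than one such child does. Section 2.9 already collects most of what is needed to identify these children, and an unseen analysis plan could use it. But section 3 names the unadjusted change test, and that stated method is the one at issue.

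**Conclusion.** The point holds as a conditional matter of precision. Eligibility allows pre-diet baselines, and the stated test cannot separate diet-start falls from the intervention effect. Under an SD of change of 100, pre-diet baselines of 1200-1800 and 23 per arm, one such child costs about 3-4 points of power, two cost 7-8 and four cost 12-16 (0.90 − 0.78 for an even split to 0.90 − 0.74 averaged over splits). If the pre-diet values are lower, as in mild PKU, the loss is smaller. With none, there is no loss. The true number cannot be learned from the article. The case for acting is that the stated analysis is the weaker choice and the better one uses data almost wholly collected already.

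**What to change.** Record diet status at month 0 (newly diagnosed or established). It can largely be derived from the age at diagnosis and historical Phe in section 2.9. Then, before outcome data are seen, replace the raw change test for Phe and Tyr with one of these:

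- **Adjusted follow-up values.** Compare 3- and 6-month values between arms, adjusted for baseline and diet status. The diet-status term is needed because one baseline slope may not fit both pre-diet and on-diet values.
- **Stratified rank test.** Use a van Elteren test stratified by diet status.

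The adjusted comparison copes better with very small numbers. In the stratified test, a stratum whose children all fall in one arm adds no information, which is certain with one child and has probability 0.49 with two.

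The cost is one extra field and slightly more analysis. Eligibility, the timing of enrolment and clinical management need no change.

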### Sample size

2.3

The sample size was calculated based on the primary metabolic indicator, serum Phe concentration. This study is a randomized controlled trial, with the intervention group receiving mobile health interventions and the control group receiving regular health education. The sample size ratio between the two groups is 1:1. According to a randomized controlled trial on PKU children based on a mobile health app (35), the blood Phe concentration in the control group was 360 μmol/L, while that in the intervention group was 260 μmol/L, with a standard deviation of 100 μmol/L in both groups. Using a two-tailed test with α = 0.05 and β = 0.1, the power (1-β) was set at 90%. Calculations performed using PASS 15 indicated that a minimum of 23 participants per group was required. Accounting for a 10% attrition rate, each group was expanded to 25 participants, resulting in a total minimum sample size of 50 participants.

### Randomization, allocation, and blinding

2.4

This research project is a single-blind, single-center randomized controlled trial to be conducted at Inner Mongolia Maternity and Child Health Care Hospital, Inner Mongolia, China. A simple random sampling method is employed for children diagnosed with PKU at our hospital. Excel software is used to create random number sequences. Participants are divided into two groups (the experimental group and the control group) using the envelope approach, which is based on the sorted order of these numbers. Randomly numbered pieces of paper are put into sealed envelopes. After being enrolled, participants open their own envelopes and discover their group assignment after receiving them in the correct order based on their given numbers. A committed staff member supervises and records the envelope distribution and opening, and safely preserves unused envelopes to maintain the integrity of allocation concealment and the single-blind design of the study.

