### Development of mHealth intervention based on the Multi-Theory Model

2.6

The Multi-Theory Model, which was created by combining the BCW theory and the Family Health theory, will serve as the foundation for the study. Using the WeChat, a mobile health intervention program will be developed for families of PKU children (including the children and their parents’ caregivers, such as parents) to explore its effectiveness in the health management of PKU children, including metabolism, nutrition, and intellectual development. According to the specific stages of applying the BCW theory, the intervention strategies for PKU families are as follows:

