### Outcomes

2.8

Primary Outcomes:serum phenylalanine and tyrosine levels in children with PKU.

Secondary Outcomes:

Nutritional indicators: Height/length (cm), weight (kg), head circumference (cm), the concentration of hemoglobin, prealbumin, albumin, complete blood count (red blood cells, white blood cells, platelets), serum iron, ferritin, and 25-Hydroxy vitamin D3.Intellectual development indicators: For children aged ≤6 years, professional physicians will use the 0–6 Years Child Developmental Behavior Assessment Scale for evaluation. For children aged >6 years, IQ will be assessed using the Chinese version of the Wechsler Intelligence Scale for Children, Fourth Edition (WISC-IV).

In addition, considering that the health management of children with PKU may impose psychological and quality-of-life burdens on their parents’ caregivers (37, 38), the study also focuses on the following indicators for parents’ caregivers: PKU disease knowledge, compliance, mental health, family health, and family atmosphere, etc. Specific details are as follows:

Changes in PKU knowledge.Changes in parental compliance with health management: Measured by the number of dietary Phe concentration logs and the number of blood tests during the intervention period (39).Impact of health management on parental mental health: Includes levels of anxiety and depression, self-efficacy, and parenting stress.Changes in the family environment of PKU children: Includes specific behavioral changes such as family communication and broader indicators such as family health.

Socio-demographic variables will be collected from patients at baseline. Clinical reagent testing and questionnaires will be conducted at baseline as well as at 3 and 6 months of follow-up, with data collection times shown in **Table 2**.

**Table 2 T2:** Data collection components and collection timeline.

Type of research	Data collection		Timepoint		
			0M	3M	6M
Quantitative research	Sociodemographic variables	Gender, age, parental education level, parental occupation, monthly household income per capita, only-child status, presence of other PKU patients in the family	✓		
	Anthropometric variables	Serum phenylalanine(Phe)and tyrosine(Tyr)levels, height/length (cm), weight (kg), head circumference (cm), the concentration of hemoglobin, prealbumin, albumin, complete blood count, serum iron, ferritin, and 25-Hydroxy vitamin D3	✓	✓	✓

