### Data collection

3.1

In this study, all data were gathered by professionally trained physicians from the Inner Mongolia Maternity and Child Health Care Hospital. These physicians conducted assessments of metabolic, nutritional, and intellectual development levels in PKU patients in strict adherence to the protocol guidelines. They also provided on-site assistance to families to help them complete the questionnaires. Furthermore, each family of PKU patients was assigned a unique code and registered to ensure that data from all follow-up points were accurately recorded on the pre-designed subject registration forms. The forms included fields for date and signature at the end to facilitate review and retrospective verification. Lastly, during the data analysis phase, a second review was conducted to identify and exclude any illogical or incomplete data entries.

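### The protocol contradicts itself on the unit of randomisation (child in 2.4, family in 2.1 and 3.1) and has no rule for siblings, so a household could be split across arms

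*Protocol article*

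**What the plan says.** The protocol article names two different units.

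- **Child or participant.** Section 2.4, the only text on how allocation is carried out, opens with "A simple random sampling method is employed for children diagnosed with PKU at our hospital". It then says that "participants open their own envelopes and discover their group assignment". It mentions neither families nor siblings.
- **Family.** Section 2.1 says "The study population consists of families of children with PKU, who will be divided into two groups". Section 3.1 says "each family of PKU patients was assigned a unique code and registered".

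The other relevant passages are these:

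- Section 2.2 defines who takes part: "The participants of this study are all PKU children and their parents’ caregivers, such as parents, who meet the inclusion criteria". The age range is 0 to under 12 years, and nothing limits entry to one child per family.
- Section 2.6 places the intervention at household level: "a mobile health intervention program will be developed for families of PKU children". Section 2.1 denies the control group the online education, reminders and consultation.
- Table 2 in section 2.8 lists "presence of other PKU patients in the family" as a baseline variable.
- Section 3 states: "The Mann-Whitney U test will be used to compare changes in each indicator between the two groups". No family term is mentioned, and section 2.3 counts participants without any allowance for relatedness.

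**The concern.** PKU is inherited, and the trial takes every eligible child at one hospital. Two siblings under 12 could therefore both qualify. The protocol does not say whether they would receive one envelope or two.

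With two envelopes, one caregiver can have a child in each arm. That caregiver sits in the intervention WeChat group, so the control condition of section 2.1 cannot be delivered to the other child. The contrast in phenylalanine (Phe) shrinks. Knowledge, PHQ-4, self-efficacy, parenting stress, family communication and family health are measured on the caregiver or the family, so for that household they belong to no single arm. One split household is enough to cause this, and no analysis can undo it afterwards.

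With one envelope, the split cannot happen. The siblings' results are still correlated, however, and the named test takes every observation as independent. A shared caregiver's scores would also count twice if they were entered once per child.

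**Working it through.** **1. The plan's own figure.** Section 2.3 gives means of 360 and 260 μmol/L (difference 100), SD 100 in both groups, two-sided α = 0.05 and 90% power. A two-sample t-test based on the noncentral t distribution has power 0.8997 at 22 per group and 0.9125 at 23. The stated 23 is reproduced, and it assumes independent participants. At the planned 25 per group, with no siblings, power is 93.4%.

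**2. Chance that a pair is split under child-level allocation.** With 25:25 among 50 children, once one sibling is placed, 25 of the other 49 places are in the opposite arm: 25/49 = 0.510. (Unrestricted 1:1 allocation would give 1/2.) The chance of at least one split among m pairs is about 1 − (1 − 0.510)^m:

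| Enrolled pairs | At least one split | Expected splits (m × 0.510) |
|---|---|---|
| 0 | 0% | 0 |
| 1 | 51% | 0.5 |
| 2 | 76% | 1.0 |
| 3 | 88% | 1.5 |
| 5 | 97% | 2.6 |

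**3. Cost of a split pair to the Phe comparison.** Assume the worst case, in which the control sibling gains the full 100 μmol/L. Each split pair moves the control mean by 100/25 = 4 μmol/L. For k split pairs the standardised difference is (100 − 4k)/100, and the noncentrality is that value × √(25/2):

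| Split pairs | Difference (μmol/L) | Power at 25 per arm |
|---|---|---|
| 0 | 100 | 93% |
| 1 | 96 | 91% |
| 2 | 92 | 89% |
| 3 | 88 | 86% |

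Partial contamination costs less. The calculation holds the SD at 100 and ignores correlation between the split siblings.

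**4. Same-arm siblings analysed as independent.** Let s be the share of children with an enrolled sibling and ρ the sibling correlation. The variance of the difference rises by the factor 1 + sρ, and the true error rate is about 2[1 − Φ(1.96/√(1 + sρ))]. The documents give neither s nor ρ; ρ = 0.5 is assumed.

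- Three pairs: s = 6/50 = 0.12, factor 1.06, error rate 5.7%.
- Five pairs: s = 10/50 = 0.20, factor 1.10, error rate 6.2%.

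Simulations give 5.7% to 5.8% and 6.2% to 6.4%. Over the wider range s = 0.05 to 0.30 and ρ = 0.3 to 0.8, the factor is 1.015 to 1.24 and the error rate about 5.2% to 7.8%.

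Steps 3 and 4 are for a comparison of means, as in section 2.3. The planned rank test would behave similarly but not identically.

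**The case against.** The best reply is that the protocol never clearly randomises individual children. The sentence naming children speaks of sampling. The allocation sentences speak of participants, and section 2.2 counts children and caregivers together as participants. Sections 2.1 and 3.1 both work by family. One envelope per family is a natural reading, and under it no household is split. This stands, and for that reason the point is a contradiction and not a finding that children are randomised individually. It does not remove the problem, because two siblings with one caregiver could still be taken as one participant or as two.

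The second reply is that siblings may never enrol. A reader might infer from the Table 2 variable that the plan expects enrolled sibling pairs. It does not show that: the other patient could be a parent, a sibling aged 12 or over, or a relative outside the trial. This also stands, so the range starts at zero pairs.

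Third, a reader might infer that power would fall below 80%. That takes five split pairs (79% at 25 per arm), which at 51% per pair means about ten enrolled pairs, or 20 of 50 children. Nothing in the protocol supports such a number. The 50 is also a stated minimum, not a fixed size.

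Fourth, handling of clustering is often left to the analysis plan, and the family codes may well mean one caregiver record per family. This is fair, and a missing cluster term alone would not be a finding. The unit of randomisation is different. It must be settled before envelopes are opened, and the passages shown disagree on it.

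**Conclusion.** The protocol is inconsistent on what is randomised, and one of its two readings can put a single caregiver in both arms. That deserves correction.

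Its size depends on the number of enrolled sibling pairs, which is not given. With none, there is no effect. With one to three split pairs and full contamination, power at 25 per arm is about 91% to 86% instead of 93%. With family allocation and an independent-data analysis, the error rate is about 5.7% to 5.8% with three pairs and 6.2% to 6.4% with five, assuming a sibling correlation of 0.5. These are modest effects on the Phe comparison. The loss of a defined arm for caregiver and family outcomes is the more awkward consequence, since one split household causes it.

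It would go too far to say that the trial is invalid on either reading. Under family allocation the excess error is small and can be handled in the analysis.

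**What to change.** In section 2.4, name the family as the unit of randomisation: one envelope per family code (the code already described in section 3.1), with every eligible child in that family following its arm. Make the wording of section 2.1 match.

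In section 3, state that caregiver and family outcomes are entered once per family. Analyse child outcomes either with one index child per family, named in advance, or with family as a cluster (robust standard errors or a random family intercept).

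The change takes about one sentence in each section and needs no extra patients or visits. The arms may differ by a child or two, and sibling data carry slightly less weight than independent data.
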